## Abstract

**Background:**

Preterm birth is the leading cause of mortality and disability in newborn and infants. Having a short cervix increases the risk of preterm birth, which can be accessed by a transvaginal ultrasound scan during the second trimester. In women with a short cervix, vaginal progesterone and pessary can both reduce this risk, which progesterone more established than cervical pessary. The aim of this study is to compare the use of vaginal progesterone alone versus the association of progesterone plus pessary to prevent preterm birth in women with a short cervix.

**Methods:**

This is a pragmatic open-label randomized controlled trial that will take place in 17 health facilities in Brazil. Pregnant women will be screened for a short cervix with a transvaginal ultrasound between 18 ^0/7^ until 22 ^6/7^ weeks of gestational age. Women with a cervical length below or equal to 30 mm will be randomized to the combination of progesterone (200 mg) and pessary or progesterone (200 mg) alone until 36 + 0 weeks.

The primary outcome will be a composite of neonatal adverse events, to be collected at 10 weeks after birth. The analysis will be by intention to treat. The sample size is 936 women, and a prespecified subgroup analysis is planned for cervical length (= < or > 25 mm).

Categorical variables will be expressed as a percentage and continuous variables as mean with standard deviation. Time to delivery will be assessed with Kaplan-Meier analysis and Cox proportional hazard analysis.

**Discussion:**

**I**n clinical practice, the combination of progesterone and pessary is common however, few studies have studied this association. The combination of treatment might act in both the biochemical and mechanical routes related to the onset of preterm birth.

**Trial registration:**

*Brazilian Clinical Trial Registry* (ReBec) RBR-3t8prz, UTN: U1111–1164-2636, 2014/11/18.

## Background

Preterm birth (PTB), defined as birth before 37 weeks of gestation, is in quantity and in severity one of the most important issue in obstetric care in the world. Globally, around 15 million preterm births are born every year [1]. In 2014 the United States it was 9.5% in 2014, while in Brazil, according to the national registry of living births system (SINASC), PTB rate was 9.9% in 2012 [2, 3]. The recent WHO report Born too Soon estimates the number of preterm births in Brazil to be 279,300 (9.1% of live births) [1]. Its prevalence has increased by 30% in the last 30 years and Brazil features among the top-10 countries with the highest numbers of preterm births [4]. Some data suggest that the real prevalence of preterm birth in Brazil approaches 10% [5].

Being born premature increases the risk of death by other causes as infections and is associated with lifelong sequelae such as cerebral palsy, visual deficiency and lower school performance [6]. Prematurity is the major cause of neonatal deaths worldwide and the second most important cause in children under 5 years, after pneumonia. Only in 2010 prematurity was responsible for 35% of 3.1 million neonatal deaths [4].

PTB is a multifactorial condition. The increase in maternal age at conception, multiple pregnancies, and maternal and neonatal related conditions are some of these factors that lead to therapeutic and spontaneous preterm labor. Women with previous PTB, preterm premature rupture of membranes (PPROM), and preterm labor also have a higher risk of PTB [7]. Even knowing some of the causes, almost 50% of the spontaneous PTB have no identifiable cause [7] and a significant reduction of PTB rates has not been accomplished so far.

One raising strategy to reduce PTB is to pay attention to physiological modifications that precede preterm labor in the uterine cervix: the cervical length shortening [8]. There is an inverse relationship between mid-trimester cervical length and the risk of preterm birth that varies as a function of the gestational age at the time the cervical shortening is diagnosed [6].

The process of cervical effacement begins some weeks before preterm labor and cervical shortening diagnosed between the 16th and 24th weeks is an important etiological factor for preterm delivery [9]. This has been demonstrated in populations with different risk profiles, varying from asymptomatic women with low-risk singleton pregnancies to women with high-risk pregnancies due to previous preterm birth or a twin pregnancy [10–12].

The best way to identify cervical shortening is by using transvaginal ultrasound examination performed between the 16th and 24th weeks of gestation. Although the cut-off limit for the cervical length that represents a risk for preterm delivery is subject to debate, the relative risk of preterm delivery among women with cervical length below the 25th percentile (30 mm) was shown to be at almost 4 times higher than for those above 40 mm [13].

Today, strategies to predict PTB include sonographic measurement of the cervical length. The shortening of cervical length is a common pathway leading to preterm labor. The shorter the cervix, the greater the risk of PTB, therefore, there may be an important role to screen for risk of preterm birth using cervical shortening [8]. Cervical length measure is best accessed by transvaginal ultrasound scan between 16 and 24 weeks and can be performed along with the routine second-trimester ultrasound [14].

When a short cervix is diagnosed during the second trimester, maternal use of progesterone reduces the rate of PTB with 30–45% [15–17]. A meta-analysis [15] indicated progestational agents generated lower rates of preterm delivery in women with a short cervix (26.2% vs 35.9%; OR 0.45, 95% CI 0.25–0.80). Relative to women allocated to receive placebo, those who received progestational agents also had lower rates of perinatal mortality (14.8% versus 17.1%; OR 0.69, 95% CI 0.38–1.3).

Progesterone can be used as either intramuscular (17 alpha-hydroxyprogesterone caproate 250 mg), subcutaneous (progesterone 25 mg), vaginal gel (progesterone 80 mg) or vaginal capsules (micronized progesterone 200 mg) but there is some evidence that vaginal progesterone is superior to other presentations to prevent PTB [18], and seems to be safe for the mother and the fetus [19]. Twin pregnancies have also a higher risk of PTB, but progesterone is not effective in unselected women with a twin pregnancy. However, the use of progesterone in patients with twin gestation and short cervix seems promising [20].

Another promising intervention to prevent preterm delivery is the use of a cervical pessary. The pessary seems to exert its effect through mechanically changing the cervico-uterine angle, reducing the compression of the cervix and protecting the cervical mucus [21]. Studies in both twins and singletons have indicated that the cervical pessary may be an effective intervention in the prevention of spontaneous preterm birth and the harm resulting from it.

Although some studies have failed to demonstrate benefits of the pessary for PTB both in singletons and twins [22–26], others [27–30] have shown a significant reduction in PTB rate in women with short cervix using a pessary. The PECEP trial was the first well-conducted randomized control trial [27] showing that in women with a short cervical length, the use of a cervical pessary reduces the preterm birth rate.

In summary, treatment with both pessary and progesterone might be helpful in reducing the rate of preterm birth. Both interventions have shown to be safe and reliable, as no maternal or fetal severe outcomes due to the use of these interventions have been demonstrated. However, the combination of progesterone and pessary for the prevention of PTB has not been tested yet. A combination could guide both pathways: the biochemical (progesterone) and mechanical (pessary), making the combined treatment more effective than a single treatment, acting in a broader set of women at risk for PTB [31, 32].

The aim of this study is to compare the effectiveness of the use of progesterone alone versus the combination of progesterone plus pessary to prevent PTB in women with short cervical length.

## Methods

This is a pragmatic, multicentre, open-label randomized controlled trial (RCT), testing the effectiveness of pessary plus progesterone versus progesterone alone in reducing preterm birth and a composite of neonatal adverse events.

### Governance

The coordinating center of the study is the Women’s Hospital at the University of Campinas in Brazil. There are 17 reference obstetric units in different geographic regions of Brazil as participating centers, including academic and general maternity hospitals and other health facilities such as ultrasound clinics and prenatal care units. The study participating centers are all members of the *Brazilian Network for Studies in Reproductive and Perinatal Health*. Each center has a local investigator, who may also select research assistant medical doctors to proceed with the intervention.

The study will be overseen by a Steering Committee (SC-P5) and a Data Safety and Monitoring Board (DSMB-P5). The SC-P5 is composed of the principal investigators, researchers of recognized national and international competence, a representative of an NGO dealing with preterm birth patients and members of the funding agencies (Bill & Melinda Gates Foundation, National Council for Scientific and Technological Development (CNPq) Ministry of Health) to evaluate the progress of the study and suggest changes when necessary.

The DSMB-P5 is composed of researchers of recognized national and international competence without any participation in the study group with the support of a statistician. This committee has complete access to the database and will meet at prespecified moments.

The Brazilian National Review Board (CONEP) approved the study under the number 1.055.555. Each local Institutional Review Boards also approved the study protocol. Protocol modifications will be reported to each relevant part including national and local institutional review boards and will be available to trial participants through the project website, to the investigators by an internal bulletin, to the registries and journals by publications, and to regulators by the review board report. No funding agency had any influence on the design and decision regarding data collections, managements, analysis and writing.

### Trial organization

A Standard Operation Procedure with video classes was developed, provided to all centers and available online, with information on how to collect and store data, how to proceed with randomization, follow-up, and outcomes. The number of subjects will be monitored weekly by the project coordinators, monitoring visits to the other participating centers twice a year. The reports from this monitoring process will be available to the monitoring committees and to the centers themselves to document the need for improvement.

The research assistant will collect informed consent before submitting the participant to the ultrasound scan, and in case of the short cervix, another consent will be applied before the randomization. Data will be kept confidential during the study. The name and the personal information will be stored in a database different from the main results and will be available only to each respective local coordinator during the follow-up. After the end of the study personal data will be split from the clinical results and will be available only to the principal investigator (PI).

The final dataset will be available to the PI and collaborating researchers. If necessary, participants will receive ancillary and post-trial care, as compensation if there is any harm secondary to the participation on the trial. The PIs do not have any competing interests for the trial. Trial results will be published as scientific articles, and authorship eligibility will be considered according to the *International Committee of Medical Journal Editors* recommendations. Participating centers are listed in Fig. 1.

**Fig. 1 Fig1:**
[figure not shown]
Participating centers and location

### Inclusion and exclusion criteria

We will study women with a singleton or twin pregnancy. Pregnant women, no maternal age restriction, at a gestational age between 18 ^0/7^ and 22 ^6/7^ weeks will be offered cervical length measurement by ultrasound (US). Women with a cervical length below or equal to 30 mm (but more than 5 mm) are eligible for the trial.

Exclusion criteria are painful contractions, vaginal bleeding, cerclage during current pregnancy before the screening, PPROM, severe liver disease, cholestasis during this pregnancy, previous or current thromboembolism, placenta previa, cervical dilation greater than 1 cm, monoamniotic twin pregnancy, higher order twin pregnancy (triplets or higher), major fetal malformation of at least one fetus and stillbirth.

### Ultrasound training

All participating members of the research team are trained to perform the cervical measurement by ultrasound and to manage the pessary. All sonographers are trained in cervical measurement according to The Fetal Medicine Foundation training program [33] and are encouraged to follow its certification program. Additionally, an online training program (using Moodle platform) was created to certificate all sonographers involved in the P5 study in standardizing cervical measurements, and at this Moodle platform, all participants of the research had signed the disclosure of contractual agreements that limit such access for investigations. The ultrasound examination will be performed using a GE Logic C5® equipment.

### Recruitment and enrolments

A research assistant will invite women attending the ultrasound department of each institution or outpatient clinics involved in the study to participate in the screening strategy and, after being informed about the study, to sign a written Informed Consent Form. A transvaginal ultrasound scan to measure cervical length as described above will be performed.

Women with a short cervix and without any exclusion criteria will then be invited to participate in the randomized clinical trial. After being informed about the study verbally and with a written patient information leaflet, women will be asked to sign an Informed Consent Form. Only after written informed consent, the local investigator will randomly assign patients. In case of an eligible participant under 18 years old, a consent form will be signed for both the underaged participant and his/her legal guardian/parent before been admitted into the study.

### Randomization

After written informed consent, women will be randomized into two groups: the use of pessary plus progesterone or the use of progesterone alone. Randomization will be stratified by center, number of fetuses (one or two) and cervical length (< 25 mm or 25-30 mm) using a 1:1 ratio and variable block sizes. Randomization is performed electronically in an online database added as a specific form in the online data collection system, using computer-generated random numbers. The system can be accessed 24/7 and a phone number is available to help the inclusion and randomization process. Each local coordinator will be responsible for the randomization process including enrollment and assignment of women to interventions.

### Interventions

Since the use of the pessary cannot be blinded, this is an open-label RCT. The pessary used is an Arabin type pessary registered at the national health surveillance agency of Brazil (Pessário AM® by Ingamed) with the dimensions: inner circle 30 mm; outer circle 70 mm; height 25 mm.

A physician trained specifically for pessary placement will insert the pessary up to 72 h from the randomization. An ultrasound scan to re-assess cervical length and pessary placement will be performed after its insertion.

We will use 200 mg micronized progesterone capsules that will be self-administered digitally inserted into the vagina every night. Commercial Progesterone (Utrogestam®) pills will be purchased from Besins Healthcare Pharmaceutics. Both interventions will be maintained until 36 weeks gestation unless antenatal care providers consider the need to withdrawal earlier.

The intervention will be discontinued before 36 weeks only if the assistant medical doctor judges it is necessary due to clinical conditions, or in case of woman request. Every enrolled woman will receive access to a P5 phone number for her to call in case of doubts or need to report side events. A research assistant will be full time available for solving such questions.

Women with threatened preterm labor will be treated with tocolysis, corticosteroids and magnesium sulfate according to local protocols.

### Follow-up

Prenatal care will continue in each reference facility considering local protocols. In each visit, the participant will be asked about the use of progesterone and pessary, symptoms, adverse events, and admission to hospital. She will receive enough progesterone until the next appointment when more capsules will be delivered. One research assistant per center will follow up all enrolled women avoiding double data collection. Adherence monitoring will be checked in all visits with the woman returning her drug table.

All enrolled women will be followed-up until 10 weeks after birth. To avoid a loss to follow-up, participants will be contacted by telephone if they miss an appointment. Compliance will be measured by the number of progesterone pills returned by the subject at each antenatal care visits.

### Outcomes

Our primary outcome is a composite of neonatal adverse events: periventricular leukomalacia (focal periventricular necrotic and diffuse gliosis in the surrounding cerebral white matter that may have cystic lesions secondary to necrotic foci in the white matter) [34], severe respiratory distress syndrome (grunting, retractions, or other typical distress symptoms in a premature infant immediately after birth with a chest radiography showing homogenous opaque infiltrates and air bronchograms) [35], bronchopulmonary dysplasia (infant requiring treatment with > 21% oxygen for at least 28 days) [36], periventricular hemorrhage grade II (hemorrhage is present in a nondistended lateral ventricle) or higher [37], necrotizing enterocolitis (spectrum of intestinal conditions including feeding intolerance, mild abdominal distention, spontaneous intestinal perforations and intestinal necrosis) [38], proven sepsis before discharge (generalized bacterial infection occurring within the neonatal period up to 4 weeks beyond the expected date of delivery accompanied by a positive blood culture) [39], stillbirth, or neonatal death.

Secondary outcomes will be gestational age at birth, birth weight, adequacy of birth weight for gestational age, first and fifth minute Apgar score, neonatal gestational age, overall, spontaneous and medical induced PTB rate before 28, 32, 34 and 37 weeks of gestation, PPROM rate, neonatal intensive care unit (NICU) admission and length of stay, maternal morbidity and mortality, maternal length of stay in hospital, maternal ICU admission, cost-benefit analysis of the screening program, treatment cost, maternal inpatient treatment costs, neonatal inpatient treatment costs and pessary use unwanted effects [40, 41].

Information on readmissions of mother and/or newborn and primary and secondary outcome will be collected during hospitalization for birth and at 10 weeks after due date, by telephone contact and patient’s registries review.

### Sample size

Considering the reduction in the risk of preterm delivery by the pessary described by the PECEP clinical trial [27], and considering our own outcomes in women with a short cervix, we anticipate a composite poor neonatal outcome rate of 22%. We consider a reduction of 10% as clinically relevant. The reduction from 22 to 12% in the composite poor neonatal outcomes (2-sided alpha 0.05, 80% power) can be detected if 438 women are randomized (219 per group). To assure a subgroup analysis for cervical length less than or equal to 25 mm, considering a reduction of 50% in adverse neonatal outcomes (17.3 to 8.65% [15]), it will be necessary to increase a sample to 468 women (234 per subgroup). Thus, the final sample should be composed of 936 women (468 in each group, 234 per subgroup).

### Data collection

The data will be collected using an online database, which is a new generation of application systems that allow the collection and cleaning of clinical trial data using the Internet. This technology was developed specifically for the study using an existing certified platform for medical offices management. The online database has distinct permission levels and is encrypted and protected by a personal security password. Data will be stored in cloud network and a backup is being performed every day.

The forms and the randomization process are inserted in the platform and access is given to each facility coordinator and research assistant for local data management. Each local coordinator is responsible for data entry. Data will be collected in printed forms or directly in the online form, available in the same online database where the randomization takes place, by a trained research assistant. The local coordinator will verify these data in the printed and online system, to assure the information is correct.

### Data analysis

Data analysis will be performed according to the intention-to-treat principle. A statistical analysis plan will be finalized prior to the data lock.

Categorical variables will be expressed by the relative frequency on the corresponding allocation arm. For continuous variables minimum, first quartile, median, third quartile, maximum, mean, and standard deviation will be presented. Missing values will be reported for all variables.

The primary outcome is a binomial random variable. For this outcome, we will estimate a risk ratio (RR) with 95% CI. We will also calculate rates in the two groups as well as the number needed to treat (NNT). The comparisons of treatments will be performed with a generalized linear model [42], with the log link function. The model will include treatment as main effect and a full factorial of study center, type of pregnancy (twin or singleton) and cervix length (two categories). The main analysis will be performed using stratums according the randomization process. All factors are fixed. The factors study center, type of pregnancy and cervix length figure as randomization block terms.

An additional model including cervical length as continuous covariate will also be analyzed. The model better adjusted will be used as final model. The Akaike Information Criterion (AIc) e Bayesian Information Criterion (BIC) will be used to decide among models. To evaluate the potential efficacy of the pessary, a per-protocol analysis will also be performed.

Secondary outcomes will be analyzed using generalized linear models with treatment as main effect and a full factorial of study center, type of pregnancy (twin or singleton) and cervix length (two categories). All factors are fixed. An appropriated link function will be chosen to each response variable.

An additional model including cervical length as continuous covariate will also be analyzed. The model better adjusted will be used as final model. The Akaike Information Criterion (AIc) e Bayesian Information Criterion (BIC) will be used to decide among models.

Survival analysis to assess time to delivery will also be performed using Kaplan Meier and Cox Proportional Hazard Model. Differences in treatments among subgroups will be assessed including in the statistical models already described above a subgroup variable and a interaction term subgroup-treatment. These are the subgroups to be analyzed:
Singleton and twin pregnanciesCervical length (≤25 mm / > 25 mm)Nulliparous/ multiparousPrevious spontaneous preterm birthObstetric US abnormalities or sludge at randomizationEthnicity (white / non-white)

The DSMB-P5 will meet at predetermined intervals (after half of the randomized cases and after 2/3 of the randomized cases) to analyze the results regarding the possible adverse effects of the interventions or regarding the achievement of statistical significance for the main outcome. Other interim analyses will be calculated according to DSMB-P5 request. The committee will have the power to recommend completion of the study or an early interruption based on the evaluation of the interim results and on some pre-specified stopping rules.

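### The stated models for infant-level secondary outcomes make no provision for correlation between co-twins, and the protocol does not say how a twin pregnancy counts in the primary composite

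*Protocol article*

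**What the plan says.** All references are to the protocol article.

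- **Population** (Inclusion and exclusion criteria): "We will study women with a singleton or twin pregnancy".
- **Unit randomised** (Randomization): "After written informed consent, women will be randomized into two groups". The number of fetuses is a stratification factor: "Randomization will be stratified by center, number of fetuses (one or two) and cervical length (< 25 mm or 25-30 mm) using a 1:1 ratio".
- **Primary outcome** (Outcomes): "Our primary outcome is a composite of neonatal adverse events". Stillbirth and neonatal death are among its components. There is no rule for a pregnancy in which only one twin has an event.
- **Secondary outcomes** (Outcomes): the list includes "birth weight, adequacy of birth weight for gestational age, first and fifth minute Apgar score", and also NICU admission and length of stay. These can differ between co-twins, and no per-woman summary is given.
- **Sample size** (Sample size): the 22% to 12% reduction "can be detected if 438 women are randomized (219 per group"). The final total of 936 is also in women.
- **Models** (Data analysis): for the primary outcome, "The primary outcome is a binomial random variable", analysed with a log-link generalized linear model. Secondary outcomes get generalized linear models with treatment plus a full factorial of centre, pregnancy type and cervical length. Both descriptions add "All factors are fixed". For secondary outcomes the link function is left open; nothing is said about variance estimation.
- **Subgroups** (Data analysis): singleton versus twin is one of the listed subgroups, tested by adding a subgroup-by-treatment interaction to these same models.

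**The concern.** Co-twins share a mother, a randomised arm and, ordinarily, a gestational age at birth, so their outcomes are correlated. Treatment is assigned to the mother. The correlation therefore falls entirely on the treatment contrast and does not cancel out within pairs.

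A generalized linear model with fixed factors and default standard errors takes every record as independent. The twin/singleton factor lets the mean differ between the two kinds of pregnancy, but it does not represent the correlation within a pair. If infants are the records, the model counts more independent information than there is. Confidence intervals are then too narrow and p-values too small, most of all where twins carry much of the information, as in the singleton/twin comparison.

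For the primary outcome the issue is different. Without a stated unit, the risk ratio, group rates and number needed to treat could refer to women or to infants, and these are different quantities. Only the per-woman version matches the sample size as worded.

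**Working it through.** **1. The plan's own figures.** For two proportions, two-sided alpha 0.05 and 80% power, with pooled variance under the null:

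n per group = [1.96·√(2·p̄·(1−p̄)) + 0.8416·√(p1(1−p1) + p2(1−p2))]² / (p1−p2)²

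- 22% vs 12%: p̄ = 0.17, so n = (1.96·√0.2822 + 0.8416·√0.2772)² / 0.01 = 221. The protocol states 219; the unpooled and arcsine versions both give 218.
- 17.3% vs 8.65%: n = 236. The protocol states 234; unpooled gives 233, arcsine 231.

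The stated sizes reproduce closely. They treat each counted unit as one independent yes/no result, contain no design effect, and name the unit as a woman. That fits one composite result per woman. At 468 women per group the power for 22% vs 12% is 0.983.

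**2. Inputs for the clustering check.** The documents give neither input, so both are assumptions:

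- t, the share of women with twins: 10-30%
- ρ, the within-pair ICC: 0.3-0.7

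The calculation applies only to infant-level outcomes analysed as if infants were independent.

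**3. Formulas.** With N women there are N(1+t) infants.

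- Design effect (DE), all infants: DE = 1 + ρ·2t/(1+t)
- Design effect, twins only: DE = 1 + ρ
- True SE / model SE = √DE
- True type I error of a nominal 5% test = 2·P(Z > 1.96/√DE)

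**4. Results.**

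| Analysis | t | ρ | DE | True/model SE | True type I error |
|---|---|---|---|---|---|
| All infants | 10% | 0.3 | 1.055 | 1.027 | 5.6% |
| All infants | 10% | 0.7 | 1.127 | 1.062 | 6.5% |
| All infants | 30% | 0.3 | 1.138 | 1.067 | 6.6% |
| All infants | 30% | 0.7 | 1.323 | 1.150 | 8.8% |
| Twins only | – | 0.3 | 1.30 | 1.140 | 8.6% |
| Twins only | – | 0.5 | 1.50 | 1.225 | 11.0% |
| Twins only | – | 0.7 | 1.70 | 1.304 | 13.3% |

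At 5% twins, the all-infants error is 5.3-5.8% over the same ICC range.

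**5. The subgroup test actually planned.** This is an interaction, not a separate test in twins. With equal variance per infant, the model variance of the interaction is proportional to 1/(1−t) + 1/(2t), and the true variance to 1/(1−t) + (1+ρ)/(2t). The ratio is DE = 1 + ρ(1−t)/(1+t).

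- Lowest corner, t = 30%, ρ = 0.3: DE = 1 + 0.3·0.7/1.3 = 1.162, type I error 6.9%.
- Highest corner, t = 10%, ρ = 0.7: DE = 1 + 0.7·0.9/1.1 = 1.573, type I error 11.8%.

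**6. Per-woman outcomes.** With one value per woman there are no pairs, so DE = 1 and the error stays at 5%. This covers time to delivery, preterm birth rates, maternal outcomes and, if so defined, the primary composite.

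**The case against.** A reader might infer that twins are treated as independent throughout, so that the primary result and every model have standard errors that are too small. The document does not support this. Nowhere does it make the infant the unit of the primary analysis. Women are randomised, the sample size is in women and reproduces as one binary result per woman, and the model factors are characteristics of the pregnancy or centre. The word binomial fits one yes/no per woman equally well. Time to delivery, preterm birth and maternal outcomes raise no pairing at all. This part of the objection stands.

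It can also be said that fixed factors describe only the named terms and do not rule out a robust variance; indeed the remedy leaves every factor fixed. That is true. The text does not contradict the remedy; it omits it. But a generalized linear model stated without any variance provision is, by default, one that assumes independence.

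The last argument is that an analysis plan, due before data lock and not shown here, may settle the matter. It may. However, the protocol does more than stay silent on secondary outcomes: it names a model, and for infant records that model is unsuitable as stated. For the primary outcome, the counting rule is needed before data lock, because the monitoring board is to look at significance for the main outcome after half and after two thirds of the women are randomised.

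Finally, the size rests on assumed inputs, and the twins-only figure belongs to a test that is not the planned one. Both points are right, which is why the interaction is worked separately.

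**Conclusion.** The point holds for infant-level secondary outcomes and their subgroup interactions. The models as stated do not allow for within-pair correlation, and on infant records they would overstate precision. Under assumed ICC 0.3-0.7 and 10-30% twin pregnancies, the true type I error of a nominal 5% test is about 5.6-8.8% overall, 8.6-13.3% in a twins-only analysis and 6.9-11.8% for the planned singleton/twin interaction. With few twins the overall effect is small.

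For the primary composite the finding is narrower: the sample size is per woman, but neither the outcome definition nor the analysis section says how a twin pregnancy counts. It should not be read as an inflated primary test, since a per-woman analysis has no inflation. The protocol should be changed, but neither the design nor the sample size is called into question.

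**What to change.** 1. In Outcomes and Data analysis, state that the primary outcome is per randomised woman, with an event if any fetus or infant has any component. This matches the sample size calculation and fixes the denominator of the risk ratio, rates and number needed to treat.
2. For birth weight, adequacy for gestational age, Apgar scores, NICU admission and NICU stay, keep the same generalized linear models and link functions, but use GEE or cluster-robust variance with the mother as cluster. Apply the same to the subgroup interaction tests on these outcomes.

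The cost is two sentences and one software option. Under the assumptions above, standard errors for infant-level outcomes grow by about 3-15% overall and 14-30% in a twins-only analysis, which only restores the correct width. Analyses with one value per woman do not change, and the sample size stays at 936.
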